### Concomitant treatments and forbidden medication

Medications applied to treat the underlying diseases, such as diabetic mellitus and hypertension, are permitted. However, new use of angiotensin-converting-enzyme inhibitors for hypertension is not permitted. Any Western medication or other Chinese medicinal therapy which can relieve cough is prohibited during the study. Additionally, antibiotics are not allowed in this study. If the participants take any forbidden medication, they will be withdrawn. Any medication used in this study must be documented in detail in case report forms (CRFs), including name, dose, dosage regimen, indication, and treatment period.

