### Outcome measures

#### Primary outcomes

Cough resolution rate: the proportion of patients whose cough is completely resolved.

Cough severity will be self-rated using a validated continuous horizontal 100-mm visual analog scale (VAS), with 0 indicating “no cough” and 100 indicating “worst possible cough” [11]. VAS value of the past 24 h will be evaluated every night at about 8:00 pm during treatment. Complete resolution of cough is defined as a reduction of VAS value to less than 17 mm [12]. Cough resolution rate across groups will be compared at days 7 and 14.
2.Cough relief rate: proportion of patients who achieve cough relief.

Cough relief is defined as a reduction of VAS value by 50% or more from the baseline. Cough relief rate across groups will be compared at days 7 and 14.

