#### Secondary outcomes

Time to cough resolution: defined as the length of time (day) from treatment start to cough complete resolution.Time to cough relief: defined as the length of time (day) from treatment start to cough relief.Change from baseline in cough symptom score (CSS) at days 7 and 14

CSS is a simple, short, and subjective tool to evaluate the overall frequency and severity of cough in the day and at night. There are daytime (from 8:00 am to 8:00 pm) and nighttime (from 8:00 pm to 8:00 am) CSS, each comprising four possible outcomes with a score range from 0 to 3 points [10]. During the trial, each patient will self-complete and record the CSS in the cough diary every day. Daytime CSS of the last 12 h will be assessed at about 8:00 pm and nighttime CSS of the last 12 h at about 8:00 am. The total CSS is the sum of daytime and nighttime CSS.
4.Change from baseline in TCM syndrome score at days 7 and 14

Each TCM symptom is graded according to TCM symptoms grading criteria (see Additional file 1). Each TCM symptom score of the past 24 h will be evaluated and graded every night at about 8:00 pm during treatment. TCM syndrome score is the sum score of the main and all minor symptoms.
5.Change from baseline in VAS value at days 7 and 146.Change of CQLQ from baseline to post-treatment

Cough-specific quality of life questionnaire (CQLQ) is a valid and reliable tool to evaluate the impact of cough on health-related quality of life [11], consisting of six domains including 28 items. The total score ranges from 28 to 112, with lower score indicating a better quality of life [13].

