### Statistical analysis

The full analysis set (FAS) includes all randomized participants who take at least one bag of ZHWFG and have follow-up data. If post-treatment follow-up data regarding the primary outcomes are missing, last observation carried forward method will be carried out to adjust for the missing data. Per-protocol set (PPS) includes patients in the FAS who comply with the protocol, are adherent to the assigned study medication, complete the visits and measurements, and have no other protocol violations. Efficacy analysis will be performed based on both FAS and PPS patients. Safety analyses include all randomized participants who take at least one bag of ZHWFG and have data for safety assessment.

An independent statistician will perform statistical analysis according to the statistical analysis plan using Statistical Analysis System (SAS) 9.4. Continuous variables will be expressed as mean (standard deviation) if the data are normally distributed, otherwise median (inter-quartile) alternatively. Categorical variables will be presented as frequency (percentage). Baseline analyses will be performed using analysis of variance or nonparametric tests for continuous variables, and chi-squared or Fisher’s exact tests for categorical variables, respectively. The primary outcomes will be analyzed using CMH-*χ*^2^ test with associated 95% confidence intervals. Time to cough resolution and relief will be analyzed using the Kaplan-Meier approach, and the difference across groups will be compared using the log-rank test. Changes from baseline to post-treatment in CSS, TCM syndrome scores, VAS, and CQLQ will be analyzed using analysis of covariance with associated 95% confidence intervals. A two-sided *P* value of 0.05 or less is considered statistically significant.

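### Change in VAS, CSS and TCM score is tested by single-time-point ANCOVA, which leaves withdrawn patients' daily diary values unused, and the handling of missing secondary values is not stated

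*Protocol article*

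**What the plan says.** All references are to the protocol article.

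- **Method (Statistical analysis).** Changes in CSS, TCM syndrome score, VAS and CQLQ "will be analyzed using analysis of covariance with associated 95% confidence intervals". No repeated-measures model is named.
- **Missing data (Statistical analysis).** "If post-treatment follow-up data regarding the primary outcomes are missing, last observation carried forward method will be carried out". Nothing is said about missing secondary values.
- **Analysis set (Statistical analysis).** The full analysis set is "all randomized participants who take at least one bag of ZHWFG and have follow-up data".
- **Measurement (Outcome measures).** For the VAS, "VAS value of the past 24 h will be evaluated every night at about 8:00 pm during treatment". For the CSS, "each patient will self-complete and record the CSS in the cough diary every day". The TCM symptoms are also graded nightly. Change in all three is compared at days 7 and 14. CQLQ has one post-treatment comparison.
- **Withdrawal (Concomitant treatments and forbidden medication).** Treatments that can relieve cough are prohibited, and "If the participants take any forbidden medication, they will be withdrawn". Withdrawal and termination criteria adds worsening of the condition as a ground.
- **Dropout (Sample size calculation).** An allowance of about 20% raises 60 to 72 per group.

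**The concern.** The data are a daily series, but each stated test uses only baseline and one later day. A patient who leaves on day 10 has ten days of scores, none of which enters the day-14 ANCOVA unless a value is filled in.

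The patients who leave are unlikely to be a random subset. The withdrawal rules select those whose cough persists or worsens, and there may be more of them on placebo. If they are left out, the placebo mean at day 14 looks too good and the ZHWFG effect is understated. If their last value is carried forward, they are denied later recovery in a condition that the Background calls generally self-limiting. The placebo mean then looks too bad, and the effect can be overstated. The reported day-14 difference would depend partly on a handling rule that the article does not give.

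**Working it through.** **The plan's own figure.** The only computed size is 46 per group for cough relief. With 70% versus 40%, two-sided α 0.05 and power 85%:

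- pooled: [1.960·√(2·0.55·0.45) + 1.036·√(0.21 + 0.24)]² / 0.30² = 47.8, so 48
- unpooled: (1.960 + 1.036)²·0.45 / 0.09 = 44.9, so 45

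The stated 46 lies between these. It does not bear on the continuous outcomes, for which the article gives no SD, correlation or dropout pattern. Those are assumed below.

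**Precision if incomplete patients were left out.** At 20% dropout, 72 × 0.80 = 57.6 per group remain. The standard error rises by √(72/57.6) = 1.118 (1.054 at 10% dropout, 1.026 at 5%). Power for an assumed 0.5 SD difference falls from 85.1% to 76.5% (81.2% at 10%, 83.2% at 5%).

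**Bias, simulation in SD units.** There were 3,000 runs per scenario, with two arms of 72.

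- Unit variances; correlation of baseline with each later day 0.4, and of day 7 with day 14 0.6.
- Placebo means 0, -1.0 and -1.6 at baseline, day 7 and day 14.
- True effect -0.30 at day 7 and -0.50 at day 14. Dropout occurs after day 7.
- The model column predicts missing day-14 values by regression on arm, baseline and day 7. It stands in for a likelihood-based repeated-measures model.

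| Dropout, placebo / active | Full data | Complete-case | Carry-forward | Model |
|---|---|---|---|---|
| Random, 20% / 20% | -0.50 | -0.50 | -0.46 | -0.50 |
| Day-7 score, same rule in both arms, 19% / 14% | -0.50 | -0.48 | -0.51 | -0.50 |
| Day-7 score in placebo, flat 10% in active, 31% / 10% | -0.50 | -0.35 | -0.70 | -0.50 |

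Relative bias from the three-decimal results:

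- Same rule in both arms, complete-case: (0.497 - 0.475)/0.497 = 4% lost.
- Placebo-driven, complete-case: (0.499 - 0.347)/0.499 = 30% lost.
- Placebo-driven, carry-forward: 0.701/0.499 = 1.40, so 40% overstated.
- Random dropout, carry-forward: 0.8 × 0.50 + 0.2 × 0.30 = 0.46, so 8% lost.

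Empirical standard errors for complete-case and model were 0.170 and 0.165, 0.166 and 0.166, and 0.172 and 0.173. The gain here is in bias, with little in precision.

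**Bias, second simulation in VAS mm.** It was built separately, with 72 per arm, a true difference of about 13-14 mm and assumed score-driven withdrawal.

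- 25% / 10% dropout after day 7: full data -13.9, complete-case -11.7 (2.2/13.9 = 16% lost), carry-forward -15.9 (2.0/13.9 = 14% overstated), repeated-measures -13.6 (2% lost).
- Across 25-30% versus 10% dropout, complete-case lost 16-27% and the model 2-3%.
- 21-22% versus 14-15% dropout driven by the daily VAS: complete-case lost 11-14% and the model about 5-7%.
- 6-14% dropout with weaker dependence: complete-case lost under 5%.

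The simulations agree in direction when score-driven dropout is concentrated on placebo: complete-case too small, carry-forward too large, the model closest to the full data.

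**The case against.** A reader might infer that the plan deletes withdrawn patients from the secondary analyses. The article does not say so. It names carry-forward for the primary outcomes without the word *only*, and never says that incomplete patients leave the ANCOVA. The full analysis set keeps anyone with one bag taken and follow-up data. Also, "An independent statistician will perform statistical analysis according to the statistical analysis plan", which is not shown and may hold the rule. That part is right: silence on the rule is not itself the fault.

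A reader might also infer that the same day-14 VAS is filled in for relief and resolution but dropped for change in VAS. That is not established. Both primary outcomes are computed from the VAS, so carrying forward the data behind them may supply the VAS change as well. Only CSS and TCM score clearly lack a stated rule.

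Other points that stand:

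- The large biases need assumed, unbalanced, score-driven dropout. The article gives one overall allowance of 20%.
- The 2.2 mm shift compares with an empirical standard error of 4.03 mm, and complete-case bias towards the null would not create a false claim of efficacy.
- Patients who leave after day 7 still count at day 7.
- Data collection and management seeks one last outcome visit at withdrawal, though this needs consent and need not fall on day 14.
- The daily VAS also feeds the time-to-event analyses, though CSS and TCM score do not.
- ANCOVA on change is a standard method.

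What remains is the stated choice of method. Neither way of treating gaps makes the single-day ANCOVA robust here. Dropping them gave -0.35 and carrying forward -0.70 against -0.50 in the adverse case, while the collected values allow an estimate close to the truth.

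**Conclusion.** The point holds as a minor one, on secondary outcomes only. The article fixes a single-time-point ANCOVA for three outcomes measured daily, and withdrawal is linked to those outcomes. The intermediate scores of withdrawn patients go unused, and how their missing values enter is unstated. The documents do not support saying that these patients are excluded, or that the VAS is handled in two contradictory ways.

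Size, all under assumed inputs: complete-case bias runs from none or under 5% (random, light or near-balanced dropout), through 11-14% in an intermediate scenario, to roughly 15-30% towards the null when score-driven dropout is concentrated on placebo. Carry-forward ran from 8% too small (random dropout) to 40% too large (the most unbalanced case). The model's good performance is partly by construction, because dropout in the simulations depended on recorded scores. None of the sizes was derived for CSS or TCM score in their own units.

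**What to change.** For VAS, CSS and TCM syndrome score, replace the separate day-7 and day-14 ANCOVAs with one mixed model for repeated measures per outcome in the full analysis set, on selected diary days that include 7 and 14 (for example 3, 7, 10 and 14). Include treatment, day, treatment-by-day, baseline value, baseline-by-day and centre, with unstructured covariance. Report each dose minus placebo at days 7 and 14 with 95% confidence intervals. Keep ANCOVA for CQLQ, and as a sensitivity analysis for the other three with its handling of missing values stated.

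The cost is analysis wording before database lock and a little programming; no new data or visits are needed. There is a small downside. The model assumes that dropout depends on recorded values. For patients withdrawn after forbidden medication, it estimates the outcome as if they had continued without it. The plan should state both.

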### Ethics and dissemination

The study protocol has been reviewed and approved by the Biomedical Ethics Committee of West China Hospital of Sichuan University (Chengdu, China). Any important modifications including the principal investigator, informed consent form, study protocol regarding eligibility criteria, outcomes and analyses, and daily diary card must be resubmitted, reviewed, and approved by the Biomedical Ethics Committee of West China Hospital of Sichuan University (Chengdu, China). Trained investigators will discuss research objective, study procedures, and potential risks and benefits with potential participants and obtain written, informed, and voluntary consent from them. Persons with impaired cognition or communication capacity who might have difficulty understanding information about the study and weighing the risks and benefits are inappropriate to participate in this study. Additionally, pregnant women or women with potential pregnancy or in lactation are excluded from the study. On the consent form, participants will be asked if they agree to use of their data. Participants will also be asked for permission for the research team to share relevant data with people from the study centers taking part in the research or from regulatory authorities, where relevant.

All participants are permitted to discontinue their participation at any time for any reason and are provided continued access to effective care. During the study period, if patients who comply with the trial protocol report any adverse reactions caused by the study medication and need to be treated, the investigators will provide timely and effective treatment freely and arrange close follow-up. Hepatic and renal functions, routine tests of blood and urine, and electrocardiogram will be measured again after treatment to monitor the adverse events. Moreover, each participant will correspond to a unique identity without any other personal identifier to maintain confidentiality. Only investigators, ethical committees, and drug regulation agencies have access to original research data. All biological specimens are exclusively collected for this specified study and will be discarded at the end of the study. This trial does not involve collecting biological specimens for storage.

The full protocol and datasets analyses of the current study are available from the corresponding author on reasonable request. The primary investigators and sponsor will communicate the trial results to participants and all the investigators involved. The trial results will be submitted to national or international conferences or peer-reviewed journals with the sponsor’s permission.

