## Background

Postinfectious cough is usually categorized as subacute cough lasting for 3 to 8 weeks and is the most common cause of subacute cough responsible for approximate 40 to 50% cases [1, 2]. Postinfectious cough usually develops and persists following respiratory tract infection, accounting for 10 to 40% cases [3, 4].

Postinfectious cough is generally self-limiting and benign; however, the protracted cough may become embarrassing and troublesome, even impairing daily life. In this case, patients may seek for medication therapy. Antihistamines, inhaled or oral corticosteroids, and central acting antitussive agents were used to relieve the cough, but treatment failure during tapering, relapse after drug withdrawal, and potential side effects may be faced [2]. Montelukast, a cysteinyl leukotriene receptor antagonist, was also found to be ineffective in this setting [5]. Inhaled ipratropium and salbutamol may reduce the cough, but the effect was short-acting [6]. Therefore, a growing number of patients turn to complementary and alternative medicine for relieve of cough.

Postinfectious cough is generally defined as exogenous cough in traditional Chinese medicine (TCM). Based on clinical practice and TCM syndrome research, wind-cold invading lungs is the most common syndrome in postinfectious cough [7]. This syndrome is primarily characterized by cough, throat itchiness, a small amount of white phlegm, and chest tightness. The general TCM therapeutic principle is to clear away wind-cold and relieve cough and to warm the lungs and reduce the phlegm.

Zihua Wenfei granule (ZHWFG) is a new Chinese herbal prescription and manufactured by Yuekang Pharmaceutical Co., Ltd (Beijing, China). Table 1 lists the detailed formula. Pre-clinical pharmacodynamic experiments (unpublished data) demonstrated that it can relieve cough and wheeze and reduce phlegm, and it also had antiallergic, anti-inflammatory, and antibacterial effects. A pilot clinical trial showed that Zihua Wenfei Zhisou decoction could alleviate the cough and was safe in treatment of postinfectious cough (wind-cold invading lungs syndrome) [8].

**Table 1 Tab1:** Formula of Zihua Wenfei granule

Pinyin name	Latin name	Family name
Ziwan	*Aster tataricus L. f.*	Compositae
Kuandong	*Tussilago farfara L.*	Compositae
Shegan	*Belamcanda chinensis L.*	Iridaceae
GanJiang	*Zingiber officinale Rosc.*	Zingiberaceae
Mangguohe	*Mangifera indica L.*	Anacardiaceae
Jingjie	*Nepeta cataria L.*	Labiatae

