### Withdrawal and termination criteria

Participants may discontinue the study prematurely at any time for any reason. The investigators will be entitled to withdraw any participant because patients develop SAE or allergic reaction, experience condition worsening, loss to follow-up, or take forbidden medications.

The National Pharmaceutical Supervisory and Administrative Department can terminate the whole study for any reason. The investigators may terminate or suspend the study due to SAE, poor efficacy, or significant deviation from the protocol during the study. The sponsors can also terminate the study because of management issues or funding problems.

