### Adverse events reporting

Adverse events refer to the unexpected medical events that occur during the study, which may not have a causal relationship with the medication. Events can be symptoms, signs, and laboratory abnormalities. Any adverse event will be recorded and reported according to standard procedures. A SAE will be defined as any medical occurrence that results in death, is life-threatening, requires inpatient hospitalization or prolongation of existing hospitalization, results in persistent or significant disability and/or incapacity, is a congenital anomaly or birth defect, or other important medical events. Other events may be considered as a SAE when the event may jeopardize the patient and may require medical or surgical intervention to prevent one of the following outcomes: death, life-threatening, or hospitalization. SAE must be reported to the Biomedical Ethics Committee of West China Hospital of Sichuan University, the sponsor, and China’s State Food and Drug Administration within 24 h.

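### Free treatment and close follow-up of study-drug reactions are promised only to participants who comply with the protocol

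*Protocol article*

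**What the plan says.** The care commitment is in the Ethics and dissemination section. It applies while the study runs, and its condition reads "if patients who comply with the trial protocol report any adverse reactions caused by the study medication and need to be treated". What those patients are then offered is that "the investigators will provide timely and effective treatment freely and arrange close follow-up". This is the only place in the article that offers either free treatment or close follow-up of a reaction.

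Other provisions are not tied to compliance:

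- In the same section, all participants may leave the study and "are provided continued access to effective care".
- Also there: "Hepatic and renal functions, routine tests of blood and urine, and electrocardiogram will be measured again after treatment to monitor the adverse events".
- Under Adverse events reporting: "Any adverse event will be recorded and reported according to standard procedures".
- Under Statistical analysis, the safety set needs one bag of granules and safety data.

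On forbidden medicines, the section on concomitant treatments states: "Any Western medication or other Chinese medicinal therapy which can relieve cough is prohibited during the study". It makes withdrawal mandatory for anyone who takes one. The Withdrawal and termination criteria section lets investigators withdraw participants because "patients develop SAE or allergic reaction, experience condition worsening, loss to follow-up, or take forbidden medications". Under Data collection and management, a withdrawn participant is asked to agree to one final visit for outcome data. Under Statistical analysis, missing post-treatment values of the primary outcomes are filled by last observation carried forward.

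**The concern.** The commitment has three conditions: the reaction is caused by the study medication, it needs treatment, and the patient complied. The first two already exclude unrelated and trivial events. The third can therefore only exclude people with a genuine, treatable harm from the drug. Whether someone the trial has injured is treated free and followed closely should not depend on adherence.

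The exclusion may also follow from the reaction itself. Allergic reactions are foreseen, and a participant who treats a rash with an over-the-counter medicine before reporting it may thereby break the protocol.

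The withdrawal rule has a second consequence. It ends scheduled observation of people who combined the study drug with another medicine, which is useful safety information. It also replaces a day-14 outcome that could have been observed with an earlier value.

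**Working it through.** **Reading the sections together.** There is no figure in the plan to reproduce, because the main point rests on wording.

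| Provision | Who is covered | Free treatment? | Close follow-up? |
|---|---|---|---|
| Treatment of reactions (Ethics and dissemination) | Compliant patients | Yes | Yes |
| General care (Ethics and dissemination) | All participants | Not stated | Not stated |
| Repeat tests (Ethics and dissemination) | No compliance condition | No | Post-treatment tests only |
| Adverse event recording (Adverse events reporting) | Any event | No | No |
| Final visit (Data collection and management) | Withdrawn participants who consent | No | One visit, for outcome data |

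Only the first row gives both benefits, and it is the only row with a compliance condition.

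**How a reaction can lead to the gap.**

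1. The ban covers any Western medicine able to relieve cough.
2. The Background says: "Antihistamines, inhaled or oral corticosteroids, and central acting antitussive agents were used to relieve the cough". Antihistamines and oral corticosteroids are thus among the medicines the article itself names as used against cough.
3. Both are also obvious choices for a rash. A participant who takes an antihistamine for a drug rash before reporting it has, on this wording, taken a forbidden medicine, faces withdrawal, and is no longer clearly a compliant patient.

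**Number affected.** The article gives the sample size (216, allocated 1:1:1) but no rate of forbidden-medicine use or of treatable reactions. The rates below are assumptions.

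- Participants on active granules: 216 × 2/3 = 144.
- If the two events are independent, expected number = 144 × P(forbidden medicine) × P(reaction needing treatment):
  - 2% and 1%: 144 × 0.02 × 0.01 = 0.03
  - 5% and 5%: 144 × 0.05 × 0.05 = 0.36
  - 10% and 10%: 144 × 0.10 × 0.10 = 1.44
- If reactions prompt self-treatment, the events are linked and the count is higher. It is at most everyone with such a reaction: 144 × 0.01 = 1.4 to 144 × 0.10 = 14.4.

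**Outcome data lost on withdrawal.** The cough visual analog scale (VAS) is rated daily over 14 days, and the primary outcomes are compared at days 7 and 14. Ratings lost = 14 − day of withdrawal. The days are illustrative.

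| Withdrawn on day | Daily ratings lost | Primary time points carried forward |
|---|---|---|
| 3 | 14 − 3 = 11 | Days 7 and 14 |
| 5 | 14 − 5 = 9 | Days 7 and 14 |
| 10 | 14 − 10 = 4 | Day 14 |

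The final visit, where the participant consents to it, does not supply the later daily ratings.

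**The case against.** The exclusion is inferred. The sentence is a promise to compliant patients; it does not say that others will be charged or left without follow-up, and the sentence before it gives everyone access to effective care. Terms of injury cover usually stand in the consent form and full protocol, which may be broader and are not shown. This has force as to consequence: nobody is denied care outright. It does not remove the point, because the article prints the compliance condition; this is not a detail lost in condensing. If the other documents are broader, the published condition should be corrected to match.

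The antihistamine example joins a Background remark to a general ban. The ban does not name antihistamines, allergic reaction is a separate ground for withdrawal, and the participant was compliant when the reaction began. It therefore remains a possible reading, not a certain one.

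On withdrawal, the article does not say outright that observation ends, and one section makes withdrawal discretionary. But seeking consent to a single last visit makes sense only if withdrawal means leaving the study. It is also true that a day-14 rating after another antitussive partly reflects that medicine. How such a value is used is a matter for the analysis plan, but collecting it keeps the choice open.

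Finally, every rate is assumed, and the article says the pilot observation showed no potential for toxicity. The upper bound of 14.4 is an extreme that needs every reactor, at a 10% reaction rate, to take a forbidden medicine.

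**Conclusion.** The concern holds. As published, free treatment and close follow-up of a drug-caused reaction are conditional on protocol compliance, and nothing in the article extends them to a non-compliant dosed participant. The gap is limited to those two benefits.

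The number affected cannot be known from the article. It is probably small: about 0.4 of 144 at 5% and 5% under independence, and higher to an unknown degree if reactions lead to self-treatment. The loss of outcome data through withdrawal is real for each person concerned, but its effect on the treatment comparison is not estimated. No sample size, power or significance level is affected. This is a low-priority, inexpensive improvement, held with medium confidence because the consent form and full protocol are not available.

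**What to change.** 1. **Ethics and dissemination:** replace the compliance condition with *participants who have taken any study medication*.
2. **Concomitant treatments and forbidden medication:** replace mandatory withdrawal with wording that forbidden medication may lead to stopping study drug, while a willing participant continues scheduled visits, diary ratings and safety tests to day 14, with the use recorded in the case report form.
3. **Withdrawal and termination criteria:** reword the forbidden-medication item to match.

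How data observed after such use enter the analysis can be left to the statistical analysis plan.

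The cost is a protocol wording amendment, a matching change to the consent form if it repeats the condition, ethics resubmission, and reaction cover and remaining visits for a small, unknown number of participants.
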